## Abstract

**Background:**

Microinstability of the hip joint is a proposed cause of hip pain and reduced function in young individuals. The underlying mechanism is thought to be extraphysiological hip motion due to bony deficiency and/or soft tissue deficiency or decreased soft tissue function. Recently, the condition has gained increased attention, and despite the fact that treatment today includes both non-surgical and surgical approaches, there is limited evidence on diagnostic specificity and treatment effects. The aim of this study is to evaluate clinical outcomes of both non-surgical and surgical treatment for microinstability of the hip joint.

**Methods:**

A multicenter prospective cohort study is planned to evaluating the outcome of physical therapy aimed at stabilizing the hip joint, as well as arthroscopic plication of the hip joint capsule, if the physical therapy fails. Outcomes will be evaluated using hip-specific patient-reported outcome measures: the short version of the International Hip Outcome Tool and the Copenhagen Hip and Groin Outcome Score, strength and function tests, health-related quality of life as determined using the European Quality of Life-5 Dimensions and the European Quality of Life-Visual Analog Scale, sports activity levels according to the Hip Sport Activity Scale, and reported complications. Patients will be evaluated at 6, 12 and 24 months after each treatment.

**Discussion:**

It is important to evaluate the clinical outcomes of both non-surgical and surgical treatment for suspected microinstability of the hip joint, and the planned prospective evaluation will contribute to the understanding of non-surgical as well as surgical treatment outcomes, including complications.

**Trial registration:**

Clinicaltrials.gov: NCT04934462. Registered June 22 2021.

**Supplementary Information:**

The online version contains supplementary material available at 10.1186/s12891-022-05269-x.

## Background

Microinstability of the hip joint is defined as extraphysiologic hip motion or pathological laxity that causes hip pain, with or without a subjective feeling of instability, and results in reduced hip function among young and active individuals [1–5]. The prevalence of hip microinstability is still unknown; however, the current data suggest that it is more common in women [6]. Hip stability depends on static and dynamic stabilizers. Static stabilizers comprise the bony morphology of the acetabulum and proximal femur, labrum, and capsular and non-capsular ligaments, with the iliofemoral ligament being the strongest ligament in the body. The negative intra-articular pressure, adhesion-cohesion, and muscle forces comprise the body´s dynamic stabilizers. Microinstability of the hip joint can be due to acetabular dysplasia, connective tissue disorders, macrotraumas, microtraumas, and iatrogenic and idiopathic causes [3]. Traditionally considered a highly stable joint, studies have shown that there is a range of translation in different hips, supporting the possible existence of hip microinstability [7–10]. In the setting of repetitive and/or forceful rotational or axial loading, this motion could stress the labrum, capsuloligamentous structures, and articular cartilage, ultimately leading to damage of the same. A unique pattern of articular cartilage damage, with inside-out abrasion, and labral- and chondral damage straight anteriorly and straight laterally has been shown to be associated with hip microinstability [11].

Treatment for hip microinstability is initiated with non-surgical treatment consisting of physical therapy that is mainly aimed at stabilizing the hip. If non-surgical treatment fails, surgery with arthroscopic plication of the hip joint capsule has yielded favorable results with low complication rates [6]. The anterior hip capsule has been shown to play an important role in hip stability, and in the applied arthroscopic technique, a plication of the capsule is performed in the region of the capsule that does not have ligamentous thickening. This is performed to tighten the hip capsule and improve the stability of the hip joint without limiting the hip’s motion or overconstraining the joint [19, 20].

An increasing body of evidence supports microinstability as a cause of hip pain; however, high-level scientific evidence supporting its role is still lacking. The current literature predominantly consists of retrospective and smaller prospective cohort studies [6, 21, 22]. It is of paramount importance that clinical decision-making is based on high-level of scientific evidence, as well as high methodological quality. The aim of the present prospective study is to evaluate the treatment outcomes of non-surgical and arthroscopic treatment for hip microinstability.

### Study objectives

The primary research objective is to evaluate the outcomes of non-surgical and arthroscopic treatments for hip microinstability using patient-reported outcome measures (PROMs) and strength and function tests up to two-years following treatment.

The secondary objectives are to evaluate health-related quality of life (HRQL), sports activity levels, and complications of non-surgical and arthroscopic treatment.

## Methods

### Study design

This is prospective cohort study will include patients ≥ 18 years of age. Patients will be evaluated clinically and radiographically at enrollment, and with PROMs and strength and functional tests at enrollment and at 6, 12, and 24 months following treatment. Patients will be recruited by experienced hip surgeons and sports medicine researchers at multiple national clinical sites. Hip function and HRQL will be evaluated using the short version of the International Hip Outcome Tool (iHOT-12), the Copenhagen Hip and Groin Outcome Score (HAGOS), the Hip Sports Activity Scale (HSAS), the European Quality of Life-5 Dimensions (EQ-5D), the European Quality of Life-Visual Analog Scale (EQ-VAS), and strength and functional tests [23–26]. Ethical approval for this study was granted by the Swedish Ethical Review Authority (#2020-05416). Written informed consent will be obtained from all the participants. This study complies with the declaration of Helsinki.

### Participant selection

#### Eligibility criteria

The inclusion criteria are as follows: 1) the patient experiences hip pain; 2) presence of at least one other finding suggestive of hip microinstability on physical examination or imaging; and 3) at least 50% reduction in pain on the Visual Analog Scale (VAS) following intra-articular hip injection of mepivacaine (10 ml, 10 mg/ml). The physical examination findings suggestive of hip microinstability that will be considered include a positive AB-HEER test, positive prone instability test, positive HEER test, Beighton score >4, and combined flexion and rotation arc ≥200°. The imaging findings suggestive of hip microinstability that will be considered are a borderline dysplasia (defined as a lateral center edge (LCE) angle of 20° to <25°, an anterior center edge (ACE) angle of 20° to <25°, and a Tönnis angle >10°–14°), a FEAR index > -5°, and a positive Cliff sign (Table 1). The LCE angle, Tönnis angle, FEAR index and Cliff sign will be evaluated using standardized anteroposterior (AP) view radiographs. The ACE angle will be evaluated using false-profile view radiographs. In addition, magnetic resonance imaging (MRI) will be performed to assess differential diagnoses. The exclusion criteria are as follows: 1) age <18 years; 2) Tönnis grade > 0 ; 3) LCE angle <20°; 4) ACE angle < 20°; 5) Tönnis angle >14°; 6) history of Legg–Calve–Perthes disease; 7) avascular necrosis of the femoral head; 8) prior hip surgery; 9) pigmented villonodular synovitis (PVNS); 10) synovial chondromatosis; and 11) other conditions that make the diagnosis of microinstability unlikely.

**Table 1 Tab1:** Inclusion criteria

Symptoms	Hip pain
Physical examination	AB-HEER test
	Prone instability test
	HEER test
	Hip flexion + rotation arc ≥ 200°
	Beighton score >4
Imaging	FEAR index > -5°
	Borderline dysplasia • LCE 20° to <25° • ACE 20° to <25° • Tönnis angle >10° to 14°
	Cliff sign
Intra-articular hip injection (mepivacaine)	At least 50% reduction of pain

The inclusion criteria are symptoms of hip pain together with at least one other positive finding on physical examination or imaging suggestive of hip microinstability and at least a 50% reduction in pain following an intra-articular hip injection of Mepivacaine. *AB-HEER* abduction-hyperextension-external rotation, *ACE* anterior center edge, *HEER* hyperextension-external rotation, *FEAR* Femoro-Epiphyseal Acetabular Roof, *LCE* lateral center edge

#### Participant recruitment

Patients will be recruited from participating center clinics. Patients are mainly referred to these clinics by other orthopedic surgeons who do not specialized in hip preservation, as well as by family medicine doctors and physical therapists. All patients who fulfill the study criteria will be considered for inclusion and asked for their consent to participate.

### Study exposure

The study groups will be defined by the given treatment and divided into groups: the non-surgical treatment only group (group 1) and the failed non-surgical treatment followed by arthroscopic treatment group (group 2).

#### Non-surgical treatment

All patients (both groups 1 and 2) will undergo six months of non-surgical treatment in the form of physical therapy aimed at stabilizing the hip joint. The physical therapy will include exercises aiming to improve and strengthen the hip musculature (see Additional file 1).

### Study outcomes

The primary outcome is hip function determined by PROMs and strength and function tests undertaken 24 months after treatment. Secondary outcomes include HRQL, sports activity levels, and treatment complications.

PROMs for hip function include the iHOT-12 and HAGOS. The iHOT-12 consists of 12 questions covering symptoms and functional limitations, sports and recreational activities, and job-related as well as social, emotional, and lifestyle concerns. The HAGOS consists of 37 questions divided into six subscales: symptoms, pain, physical function in daily living, function in sports and recreational activities, participation in physical activities, and quality of life. Both the iHOT-12 and HAGOS have been translated and validated in Swedish and have shown sound psychometric properties when used for young and active individuals with hip complaints [27, 28].

Maximal isometric hip muscle force for hip flexion, extension, adduction, and abduction will be assessed using an externally fixated dynamometer or a handheld dynamometer (Hoggan MicroFET2, Hoggan, Scientific L.L.C., Salt Lake City, USA). The maximum developed force in Newtons (N) will be recorded.

Hop performance will be measured with three single-leg hop tests: vertical hop (Muscle lab, Ergotest Technology, Oslo, Norway), hop-for-distance, and 30-second side-hop test. Each hop test is performed with the patients holding their hands behind their backs. For the vertical hop, the time from takeoff to landing is converted into hop height in centimeters (cm). In the hop-for-distance test, the distance between the tip of the toes at takeoff to the heel at landing is measured in cm. For the 30-second side-hop test, one trial per leg is allowed, where the patient will be instructed to hop as many times as possible over two lines that are 40 cm apart. The number of hops will be recorded.

HRQL will be evaluated using the EQ-5D and EQ-VAS. Sports activity level will be determined via the HSAS, which is a hip joint-specific sports activity scale that ranges from no performance of recreational or competitive sport to performance of competitive sports at national and international elite levels. The HSAS has been translated and validated in Swedish and has shown sound psychometric properties when used with young and active individuals with hip complaints [29]. All complications, including, but not limited to, stiffness, continued instability, reoperations and or conversion to a total hip arthroplasty (THA), will be documented by researchers.

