### Sample size calculation

Based on previous results of arthroscopic hip preservation surgery, for the comparison of pre- and post-treatment hip function, a minimum sample size of 26 patients for each treatment group is needed to reach a power of 80% with the iHOT-12 (sigma 25.5, alpha 0.05, effect size 20) [30].

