### Statistical plan

Changes in hip function, sports activity levels, and HRQL at 6-, 12-, and 24-month follow-ups compared to baseline within groups will be evaluated using the Wilcoxon signed-rank test. Comparisons between groups 1 and 2 will be performed using the Mann–Whitney U test. The results will be reported as numbers, distribution values, and associated *p*-values. Complications will be reported as numbers and percentages. No interim analyses are planned. The alpha value will be set at <0.05.

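### The single primary outcome at 24 months bundles at least 14 measures, none designated as primary, while power is stated for the iHOT-12 alone

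*Protocol article*

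**What the plan says.** The Study outcomes section of the protocol article uses the singular: "The primary outcome is hip function determined by PROMs and strength and function tests undertaken 24 months after treatment". It then lists the contents:

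- Questionnaires: "PROMs for hip function include the iHOT-12 and HAGOS", and "The HAGOS consists of 37 questions divided into six subscales". No HAGOS total score is mentioned.
- Strength: "Maximal isometric hip muscle force for hip flexion, extension, adduction, and abduction will be assessed".
- Function: "Hop performance will be measured with three single-leg hop tests".

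Study objectives gives the same combination as the primary objective, so this is not a slip in one sentence.

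The Sample size calculation asks for 26 patients per treatment group "to reach a power of 80% with the iHOT-12", using a sigma of 25.5 and an effect of 20. It describes this as serving the pre- versus post-treatment comparison.

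Under Statistical plan, changes in hip function at 6, 12 and 24 months "compared to baseline within groups will be evaluated using the Wilcoxon signed-rank test". Groups 1 and 2 are compared by the Mann–Whitney U test. The section closes with one threshold: "The alpha value will be set at <0.05". It gives no ordering of measures, no composite, and no rule on how many measures must agree.

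**The concern.** A primary outcome should yield one answer to the primary question, fixed before the data are seen. Here the label covers three kinds of measurement that can disagree. A patient may report better function while isometric force or hop distance does not change, and the protocol does not say what the study would then conclude.

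The sample size adds a mismatch. The planning measure is the iHOT-12, but neither the objectives nor the outcomes section gives it priority over the other 13. The stated 80% power applies to one component of the bundle, and a reader of the final report could not tell from the protocol which result was meant to come first. That leaves room for emphasis to follow significance.

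**Working it through.** **1. The plan's own figure.** Inputs from the Sample size calculation: sigma 25.5, effect 20, alpha 0.05 (two-sided assumed), power 80%. The two-independent-means formula gives n = 2 × (25.5/20)² × (1.960 + 0.842)² = 2 × 1.6256 × 7.849 = 25.5, so 26 per group, with power 80.7% at 26. The figure reproduces. The text describes a pre/post comparison, however. With a paired formula, reading sigma as the cross-sectional SD, the need is 26, 18, 13 or 8 at assumed pre/post correlations of 0, 0.3, 0.5 or 0.7. These are normal approximations. So 26 also suffices for a within-group iHOT-12 test at any non-negative correlation.

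**2. Count of measures (Study outcomes).** 1 (iHOT-12) + 6 (HAGOS) + 4 (strength) + 3 (hop tests) = 14. It is at least 14, because the section does not say whether each leg is analysed separately. If HAGOS were reduced to one score, the count would be 1 + 1 + 4 + 3 = 9.

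**3. Chance of at least one false positive.** This is for one set of 14 tests (one comparison at 24 months), each at two-sided 0.05, with no true change on any measure.

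- Independent, either direction: 1 − 0.95^14 = 0.512.
- Independent, favourable direction only: 1 − 0.975^14 = 0.298.
- With nine measures, independent, either direction: 1 − 0.95^9 = 0.370.

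Correlated measures were simulated as 14 equally correlated normal statistics (400,000 draws):

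| Assumed common correlation | Either direction | Favourable only |
|---|---|---|
| 0 | 51% | 30% |
| 0.3 | 44% | 22% |
| 0.5 | 35% | 17% |
| 0.7 | 25% | 12% |
| 0.9 | 14% | 7% |

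**4. Keeping all 14 as primary with a Bonferroni split.** Alpha per test is 0.05/14 = 0.00357. The formula that reproduces 26 then needs 46 per group, and 26 per group has 46.6% power for the iHOT-12 effect. This depends on that formula: if sigma is read as the SD of the change, the paired version needs 23.

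**5. Naming the measure alone is not enough.** At 24 months each measure can be tested within group 1, within group 2 and between groups. Naming the iHOT-12 without a comparison leaves three tests: 1 − 0.95³ = 0.143 if independent.

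**The case against.** The strongest reply is that this is an uncontrolled cohort whose objective is to evaluate outcomes. It states no hypothesis, no success criterion and no confirmatory claim, and results are to be reported with distribution values and p-values. The iHOT-12 is visibly the planning measure. Multiplicity adjustment is commonly left to an analysis plan, which is not shown.

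Much of this stands, and it rules out some stronger readings:

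- A reader might infer that the protocol lets the study declare success on any significant measure. No such rule is written. The text permits selective emphasis; it does not prescribe it.
- A reader might take it as stated that each of the 14 is tested at 0.05. That is the natural reading of one threshold applied to hip function, but the Statistical plan does not list tests by subscale or muscle direction.
- A reader might quote 51% as the error rate. It is the upper end: it assumes independence, which is unlikely for subscales of one questionnaire and forces from one hip, and it counts significant worsening. Every figure also assumes no change on any measure, whereas the sample size anticipates a 20-point iHOT-12 change.
- A reader might count 14 × 3 comparisons × 3 visits = 126 primary tests. The primary outcome is fixed at 24 months, so the earlier visits lie outside it, and the between-group test is not tied to particular visits.

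What does not stand is the appeal to an unseen analysis plan or a fuller protocol. The article does state the primary outcome, and states it as a bundle. The absence of an adjustment method is not the point here. Nor does the sample size settle the matter by implication, since the objectives and outcomes sections give strength and function tests the same primary status.

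**Conclusion.** The point holds as a fault in how the primary outcome is defined. At least 14 measures share one primary label, none is designated, nothing combines them, and power is stated for one. Conflicting results would leave the primary question unanswered.

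The size is a range: 51% down to 14% for any false positive in one set of 14 tests, or about 30% down to 7% for a favourable one, as the assumed common correlation goes from 0 to 0.9. The documents give no correlations, so no single value can be defended, but every value in the range exceeds its nominal rate (5% either way, 2.5% favourable). The rates assume no true change on any measure and a test of each measure at two-sided 0.05. The definitional fault depends on none of these assumptions.

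**What to change.** In Study outcomes, name iHOT-12 change from baseline to 24 months, tested within each treatment group, as the primary outcome and comparison. This is the comparison the Sample size calculation says the study is sized for. The 24 months should run from each group's own starting point as defined in Study follow-up. Align the primary objective in Study objectives.

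Make HAGOS, the strength and hop tests, and the between-group comparison secondary, reported as estimates with 95% confidence intervals and without confirmatory claims. State that the two within-group tests answer separate questions, one per treatment. If either alone were to count as a positive study, the error rate would be 1 − 0.95² = 9.75% under independence.

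The cost is a few sentences. The planned 26 per group, the 0.05 level and the data collection do not change. The downside is that strength and function tests lose primary status, although the Discussion gives the lack of such data as one reason for the study. Labelling them key secondary outcomes keeps them prominent. The registry record was not available to me; if it carries the same bundle, it should be updated to match.

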### Study follow-up

Patients will be followed-up for 24 months post-treatment (i.e. midterm follow-up). Group 1 will be followed-up 24 months after initiation of physical therapy, and group 2 will be followed-up 24 months after surgery. PROMs will be completed electronically by the patient at baseline, and at 6, 12, and 24 months post-treatment. Strength and function tests will be evaluated during in-person visits by physiotherapists at baseline, and at 6, 12, and 24 months post-treatment. Number of physical therapist visits will be summarized at 6 months post-treatment. Documentation of complications will be recorded at 24 months post-treatment. Non-responders will be reminded via email and telephone multiple times before being considered as lost to follow-up.

### Sample size calculation

Based on previous results of arthroscopic hip preservation surgery, for the comparison of pre- and post-treatment hip function, a minimum sample size of 26 patients for each treatment group is needed to reach a power of 80% with the iHOT-12 (sigma 25.5, alpha 0.05, effect size 20) [30].

### Statistical plan

Changes in hip function, sports activity levels, and HRQL at 6-, 12-, and 24-month follow-ups compared to baseline within groups will be evaluated using the Wilcoxon signed-rank test. Comparisons between groups 1 and 2 will be performed using the Mann–Whitney U test. The results will be reported as numbers, distribution values, and associated *p*-values. Complications will be reported as numbers and percentages. No interim analyses are planned. The alpha value will be set at <0.05.

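### The only between-group analysis is an unadjusted Mann–Whitney test in non-randomised groups; it does not fix scores or changes and makes no adjustment for the enrolment value collected for each measure

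*Protocol article*

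**What the plan says.** All references are to the Methods of the Protocol article.

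- **Statistical plan.** Within each group, changes at 6, 12 and 24 months "compared to baseline within groups will be evaluated using the Wilcoxon signed-rank test". The next sentence is the whole of the between-group analysis: "Comparisons between groups 1 and 2 will be performed using the Mann–Whitney U test". It names no covariate and does not state whether the test is applied to scores or to changes.
- **Study follow-up.** The baseline values exist: "PROMs will be completed electronically by the patient at baseline, and at 6, 12, and 24 months post-treatment", and "Strength and function tests will be evaluated during in-person visits by physiotherapists at baseline, and at 6, 12, and 24 months post-treatment". Group 1 is timed from the start of physical therapy, group 2 from surgery.
- **Study exposure** and **Arthroscopic treatment.** Groups are formed by the treatment given. Group 2 consists of patients whose six months of physical therapy failed by their own report and who then had surgery.
- **Sample size calculation.** "a minimum sample size of 26 patients for each treatment group is needed to reach a power of 80% with the iHOT-12", with inputs "sigma 25.5, alpha 0.05, effect size 20", stated "for the comparison of pre- and post-treatment hip function".

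**The concern.** A Mann–Whitney test takes no covariate. Without randomisation, nothing makes the groups equal at enrolment, and patients who start worse may plausibly be over-represented among those who still report poor function at 6 months and go on to surgery.

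Two things follow. First, precision is given away: part of the spread in 24-month scores is predictable from the enrolment score, and the planned test does not remove it efficiently. Second, a baseline gap enters the result, and how it enters depends on a choice the plan leaves open. Scores carry the gap forward; changes can carry part of it in the opposite direction. An analyst could therefore reach estimates of different sign from the same data while following the same sentence of the plan.

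This is a method the protocol names, so it is not a detail left to an analysis plan that is not shown.

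**Working it through.** **1. The plan's own figure.** Inputs from the Sample size calculation: difference d = 20, SD σ = 25.5, α = 0.05 (taken as two-sided), power 80%. The two-sample normal formula is n = 2[σ(1.96 + 0.84)/d]² per group. It gives 25.5, rounded up to **26**, so the stated figure is reproduced. (A paired calculation with 25.5 as the SD of change would give 13, or 15 by the t test.) The protocol describes the figure as pre/post, so using d = 20 as a between-group difference below is an assumption. So are equal groups of 26 and every value of the baseline-to-follow-up correlation ρ.

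**2. Power by formula.** Power = Φ(d / [SD·√(2/n)] − 1.96), with:

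- Mann–Whitney on scores: SD = 25.5, n = 26 × 3/π = 24.8
- Mann–Whitney on changes: SD = 25.5·√(2(1−ρ)), n = 24.8
- ANCOVA on baseline: SD = 25.5·√(1−ρ²), n = 26

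Example at ρ = 0.5. The ANCOVA SD is 25.5 × 0.866 = 22.08 and the standard error 22.08 × √(2/26) = 6.125, so power = Φ(3.265 − 1.96) = 90.4%. For Mann–Whitney on scores the standard error is 7.24, so power = Φ(2.763 − 1.96) = 78.9%.

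| ρ | MW scores | MW changes | ANCOVA | Gain over scores | Gain over changes |
|---|---|---|---|---|---|
| 0.3 | 78.9% | 64.6% | 84.2% | 5.3 | 19.6 |
| 0.5 | 78.9% | 78.9% | 90.4% | 11.5 | 11.5 |
| 0.7 | 78.9% | 94.6% | 97.7% | 18.8 | 3.1 |

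**3. Power by simulation** (normal data, 6,000 replicates per ρ).

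| ρ | MW scores | MW changes | ANCOVA | Gain over scores | Gain over changes |
|---|---|---|---|---|---|
| 0.3 | 77.1% | 63.1% | 82.3% | 5 | 19 |
| 0.5 | 77.2% | 76.4% | 88.7% | 12 | 12 |
| 0.7 | 76.1% | 93.3% | 96.9% | 21 | 4 |

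Rank ANCOVA, in a separate simulation of 4,000 replicates, reached 80%, 86% and 95%. That is about 2, 9 and 18 points above Mann–Whitney on scores in the same runs (78%, 77%, 77%), and about 17, 9 and 1 above Mann–Whitney on changes (63%, 77%, 94%).

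**4. Effect of a baseline gap.** Assume no treatment effect and group 2 starting 10 iHOT-12 points lower. What counts as no effect can be defined in two ways.

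*(a) Both groups regress to a common mean.* The expected error is −10ρ on scores, +10(1−ρ) on changes and 0 with ANCOVA.

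| ρ | Error: scores / changes / ANCOVA | False positives: scores / changes / ANCOVA |
|---|---|---|
| 0.3 | −3 / +7 / 0 | 6.6% / 11.9% / 5.3% |
| 0.5 | −5 / +5 / 0 | 9.9% / 11.1% / 4.5% |
| 0.7 | −7 / +3 / 0 | 15.8% / 8.4% / 5.2% |

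*(b) The 10-point gap is stable over time.* The expected error is −10 on scores, 0 on changes and −10(1−ρ) with ANCOVA.

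| ρ | Error: scores / changes / ANCOVA | False positives: ANCOVA |
|---|---|---|
| 0.3 | −10 / 0 / −7 | about 18% |
| 0.5 | −10 / 0 / −5 | about 12% |
| 0.7 | −10 / 0 / −3 | about 9% |

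In (b), scores give about 27–28% false positives and changes stay near the nominal level (4.6% at ρ = 0.5).

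On bias, ANCOVA does better than scores in both settings. Against changes it does better in (a) and worse in (b).

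**The case against.** The strongest reply is that ANCOVA is not a neutral standard in non-randomised groups. Setting 4(b) is as possible as 4(a), and there the change-score comparison is right and ANCOVA under-corrects. Stable differences in body size or sex mix behind force and hop distance are a natural example. This stands. A reader might infer that baseline adjustment makes the comparison unbiased; the documents do not support that, because nothing in them says how the groups would evolve without a treatment effect.

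A reader might also infer that the plan loses a fixed 9–12 points of power. The documents do not support that either. It needs a correlation near 0.5, which the protocol does not give, and a 20-point difference between groups, whereas the protocol states 20 points for pre/post change and claims no power for group 1 against group 2.

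Nor can it be said that baseline is certainly left out. The preceding sentence of the Statistical plan concerns changes, so a comparison of changes is a fair reading, and baseline then enters, though unadjusted.

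The between-group test is also secondary to evaluating each treatment's outcome, for which the sample size is stated. The larger threats to it are the selection of group 2 on its 6-month result and the different time origins, which adjustment leaves in place.

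These points limit the size of the claim. They do not justify a covariate-free test on an unspecified quantity.

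**Conclusion.** The concern holds in limited form. The protocol's only between-group analysis makes no adjustment for enrolment values that it collects and leaves open which quantity is compared.

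Under the stated illustration, ANCOVA gains about 5 to 20 power points over scores as the correlation rises from 0.3 to 0.7, and about 20 falling to 3–4 over changes. Rank ANCOVA gains less, down to about 2 points over scores at 0.3 and 1–2 over changes at 0.7. These figures rest on an assumed effect, assumed correlations, equal groups and normal data; they contradict no power claim in the protocol.

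On bias, the two unadjusted forms can err in opposite directions under regression to a common mean. Adjustment cures that only under the same assumption. The within-group Wilcoxon tests are not affected.

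**What to change.** In the Statistical plan, replace the Mann–Whitney sentence with a baseline-adjusted comparison at 24 months:

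- Fit an ANCOVA of the 24-month value on group and the enrolment value of the same measure. Use rank ANCOVA, or a proportional-odds model with the baseline score, for ordinal scales such as the HSAS.
- Report the adjusted difference (for a proportional-odds model, the adjusted odds ratio) with a 95% confidence interval.
- Give the between-group comparison of changes as a sensitivity analysis, since the two rest on different assumptions.
- State that the comparison is observational, and that adjustment removes neither the selection of group 2 on its 6-month result nor the different time origins.
- Keep the within-group Wilcoxon tests.

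**Cost.** A few sentences and little extra analysis; no new data, visits or patients. ANCOVA assumes a roughly linear baseline slope common to both groups and needs a non-missing baseline value. The common slope is less certain here: group 2's enrolment value lies at least 6 + 24 = 30 months before its outcome, against 24 in group 1.
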